## Abstract

**Background:**

Women undergoing in vitro fertilization (IVF) or intracytoplasmic sperm injection (ICSI) with poor ovarian respond (POR) always have very low clinical pregnancy rates. In previous data, dehydroepiandrosterone (DHEA) was suggested as a promising treatment and maybe has a good pregnancy outcome. But there is no sufficient evidence from randomized clinical trials evaluating the effect of DHEA preconceptional treatment on live birth in POR.

**Methods:**

This trial is a multicenter active-placebo double-blind clinical trial (1:1 treatment ratio of active versus placebo). The infertile POR patients undergoing IVF or ICSI will be enrolled and randomly assigned to two parallel groups. Participants in these two groups will be given 4–12 weeks’ treatment of DHEA or placebo, respectively. The primary outcome is live birth rate.

**Discussion:**

The results of this study will provide evidence for the effect of preconceptional DHEA treatment on IVF outcome in POR.

**Trial registration:**

Chinese Clinical Trial Registry, ChiCTR-IPR-15006909. Registered on November 9, 2015.

**Electronic supplementary material:**

The online version of this article (10.1186/s13063-018-3146-x) contains supplementary material, which is available to authorized users.

## Background

The management of poor ovarian respond (POR) remains a serious dilemma for fertility clinicians. The incidence of POR, which was associated with very low clinical pregnancy rate (CPR), was reported to be 9–24% [1]. Among infertile women in vitro fertilization (IVF) cycles. CPR was only 14% and the cycle cancellation rate of no available embryos was as high as 40% for women with fewer than five oocytes [2]. It was confirmed that the outcomes of IVF/intracytoplasmic sperm injection (IVF/ICSI) would be improved with increasing number of oocytes retrieved, especially for those with poor ovarian response or advanced maternal age [3].

Various approaches have been used to obtain more mature oocytes and available embryos for POR. Different stimulation protocols [4–7], increasing gonadotropin dosage [8, 9], combining pretreatment protocol [10–12], and usage of adjuvant [13, 14] have been tried in IVF/ICSI cycles. But there is no evidence from randomized clinical trials evaluating the effect of dehydroepiandrosterone (DHEA) preconceptional treatment on live birth in POR.

Androgen in the ovarian microenvironment plays an important role in early follicular development and granulosa cell proliferation. Administration of androgen was suggested as a promising treatment. Androgens can upregulate the follicular follicle-stimulating hormone (FSH) receptor expression, augment follicular sensitivity to FSH stimulation, and increase the number of antral follicles and mature oocytes [15]. Clinical observation [16] indicates that the lack of androgen is associated with low ovarian response and pregnancy rate during IVF.

The most widely used androgen in the clinic is DHEA. DHEA has low androgen activity but can transform highly active androgen *in vivo*; meanwhile, the incidence of adverse reactions is low. Numerous reports indicated that DHEA supplementation in patients with decreased ovarian reserve or POR was helpful to improve ovarian reserve parameters [17, 18], augment ovarian response [19], reduce age-related aneuploidy [20], and increase pregnancy rate [21]. However, most of the studies were based on retrospective or observational data or both. Several randomized controlled trials (RCTs) were criticized for inappropriate study design, the varied definition of POR, and duration of DHEA [22]. There is an urgent need for large-scale, well-designed confirmatory studies to prove the efficacy of DHEA before it could be recommended for routine use.

The purpose of this multicenter randomized placebo-controlled double-blind clinical trial is to evaluate the effect of DHEA treatment for 12 weeks before IVF/ICSI on the live birth rate in infertile POR.

## Methods/Design

### Study design

This study has a multicenter, randomized active-placebo, double-blind design. Eligible patients will be randomly assigned to active group or placebo group with a 1:1 ratio. Figure 1 shows a flowchart of the study design.

**Fig. 1 Fig1:**
[figure not shown]
Study flowchart

### Study sites

This clinical trial involves eight hospitals in China. Live birth rate of active group versus placebo group will be compared in a pool of 710 infertile POR patients undergoing their sequence cycle of IVF/ICSI. The study will be conducted in accordance with Good Clinical Practice guidelines and the Declaration of Helsinki. The study has been approved by the ethics committees at all hospitals and facilities.

The trial and study plan will be declared to all participants at their first visit. If patients are eligible and interested in participating, the couples will be asked to sign an informed consent form giving permission to use their results anonymously in future studies. Reporting of the study results will follow the 2010 revised CONSORT (Consolidated Standards of Reporting Trials) statement [23]. An overview of specific measurements and time points of data collection can be found in the SPIRIT (Standard Protocol Items: Recommendations for Interventional Trials) Figure (Fig. 2, Additional file 1).

**Fig. 2 Fig2:**
[figure not shown]
Standard Protocol Items: Recommendations for Interventional Trials (SPIRIT) figure

### Training of investigators

All investigators are required to undertake mandatory training in the protocol, Good Clinical Practice, and the use of CONSORT if they had no recent certifications.

#### Study population

The study will include patients with POR. Inclusion criteria are (1) women who had tried to become pregnant for at least 1 year, (2) women who will undergo IVF or ICSI, and (3) women with POR diagnosed according to the Bologna consensus [24].

Exclusion criteria are (1) women who had failed in three or more IVF cycles with ovarian stimulation and oocyte pickup, (2) women with diagnosed uterine malformation or abnormality, (3) women with diagnosed hydrosalpinx in hysterosalpingography, (4) women who had a history of two or more spontaneous miscarriages (biochemical miscarriage does not count in), (5) couples with female or male abnormal karyotype, (6) women who had undergone chemotherapy with cytotoxic agents, (7) women who had undergone pelvic radiotherapy, (8) women who had taken DHEA before enrollment, (9) women with a history of epilepsy, and (10) women who are allergic to DHEA.

### Determination of the sample size

The sample size calculation is based on the live birth rate. Data from our hospital indicated that the live birth rate of infertile POR undergoing IVF/ICSI cycles was 20%. In our present study, we plan to test the primary hypothesis of a difference of 10 in the live birth rate for the two randomization arms. A sample size of 294 prospectively enrolled participants in each randomization arm will yield a statistical power of 80 at a *P* value of less than 0.05 to demonstrate a significant difference in live birth rates of 10 between treatment arms. In consideration of a dropout rate of 20%, we will enroll 355 participants each group.

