#### Data analysis plan

Statistical analysis will be performed by using Statistical Package for the Social Sciences Version 22.0 (SPSS Inc., Chicago, IL, USA). Normally distributed continuous variables are expressed as mean ± standard deviation with a Wilcoxon rank-sum test for testing between-group differences. Non-normally distributed continuous variables are expressed as medians and ranges, and categorical data are described as frequency, percentage, and constituent ratio.

The primary analysis will use an intention-to-treat analysis approach to examine differences in the live birth rate between the two treatment arms by the Pearson chi-squared test. Secondary efficacy parameters and safety parameters (pregnancy rate, OHSS rate, and so on) will be analyzed by using the Pearson chi-squared test. The Wilcoxon rank-sum test will be performed to compare continuous parameters (retrieved oocyte number, gonadotropin dosage, E2 level on the hCG trigger day, and so on). The analysis of covariance (ANCOVA) tests will be used to compare the indicators (basic FSH, E2 level, and AMH level) pre- and post-treatment between-group, and pre-post paired *t* tests will be used within-group.

A secondary per-protocol analysis will be performed according to the actual treatment that subjects received.

Results will be presented as point estimates and 95% confidence intervals; the level of significance will be set at 5%.

The flowchart of this study is presented in Fig. 1, and the SPIRIT checklist is included as Fig. 2.

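### The 20% dropout allowance is miscalculated: 355 per arm leaves 284, not 294, so power on the plan's own assumptions is 78.7% rather than 80%

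*Protocol article*

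**What the plan says.** The Protocol article, under Determination of the sample size, builds the enrolment target in two steps.

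- **Base size.** The control rate comes from local data: "Data from our hospital indicated that the live birth rate of infertile POR undergoing IVF/ICSI cycles was 20" per cent. The hypothesis is "a difference of 10 in the live birth rate for the two randomization arms". From this it concludes: "A sample size of 294 prospectively enrolled participants in each randomization arm will yield a statistical power of 80" at P below 0.05.
- **Dropout allowance.** "In consideration of a dropout rate of 20%, we will enroll 355 participants each group".

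The total of 710 appears again under Study sites and in the Discussion, so 355 per arm is not a misprint. Under Data analysis plan the article says: "The primary analysis will use an intention-to-treat analysis approach", with a Pearson chi-squared test on live birth, and "the level of significance will be set at 5" per cent.

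**The concern.** An allowance for 20% dropout should leave the required number once 20% have been lost. Twenty per cent of 355 is 71, and 355 − 71 = 284, which is 10 short of 294 in each arm. The enrolment target therefore does not follow from the paragraph's own inputs, and the 80% power claim attached to it is not met if dropout is as assumed.

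The paragraph also treats dropouts as women removed from the comparison, whereas the primary analysis is by intention to treat. The power it quotes is thus for women remaining after dropout, not for the analysis that will carry the conclusion.

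At stake is the accuracy of two figures that readers will use to interpret the result: the planned number of women and the planned power.

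**Working it through.** **Inputs** (Protocol article, Determination of the sample size, unless noted)

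- Control live birth rate: 0.20.
- Difference: 10, printed without a unit. Read as percentage points, so 0.20 versus 0.30.
- Power: 0.80.
- Significance level: 0.05. Sidedness is not stated; two-sided is assumed because it reproduces the stated size.
- Allocation: 1:1 (Randomization and blinding).
- Test: Pearson chi-squared (Data analysis plan), taken without continuity correction.
- Dropout: 20%. Enrolled: 355 per arm.

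**Step 1: reproduce 294.** Pooled-variance formula for two proportions, with p̄ = (0.20 + 0.30)/2 = 0.25:

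n = [1.960 × √(2 × 0.25 × 0.75) + 0.842 × √(0.20 × 0.80 + 0.30 × 0.70)]² / 0.10²

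= [1.960 × √0.375 + 0.842 × √0.37]² / 0.01 = 293.2, so **294 per arm**.

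This matches exactly. Other choices do not: one-sided 231, two-sided with continuity correction 313, unpooled variance 291, arcsine 292, and a fall from 20% to 10% 199.

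**Step 2: the dropout allowance.**

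- To keep 294: 294/(1 − 0.20) = 367.5, so 368 per arm and 736 in total.
- Multiplying instead: 294 × 1.20 = 352.8. The stated 355 is near this, but the article does not say how it was obtained.
- Shortfall: 368 − 355 = 13 per arm, 26 in total.
- Left after 20% loss: 355 × 0.80 = 284 per arm.
- Largest loss that still keeps 294: 1 − 294/355 = 61/355 = 17.2%.

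**Step 3: power for 20% versus 30%.** Power = Φ{[0.10 × √n − 1.960 × √0.375] / √0.37}.

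| n per arm | Power (formula) | Power (exact enumeration of the chi-squared test) |
|---|---|---|
| 284 | 78.7% | 78.9% |
| 294 | 80.1% | 80.3% |
| 355 | 87.0% | 87.0% |

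At 284 the loss is 80.1 − 78.7 = 1.4 points against the power at 294, or 1.3 points against the stated 80%. With less dropout the target is enough: 15% loss gives 81.1% and 10% gives 83.3%.

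**Step 4: power when all 355 per arm are analysed.** Each row rests on an assumption that the article does not make.

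| Assumption about the 20% | Rates compared | Power |
|---|---|---|
| All outcomes known, effect undiluted | 20% vs 30% | 87.0% |
| Dropouts in both arms counted as no live birth | 0.8 × 20% = 16% vs 0.8 × 30% = 24% | 76.1% |
| Active-arm dropouts revert to the placebo rate | 20% vs 0.8 × 30% + 0.2 × 20% = 28% | 70.5% |

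With 368 per arm, the last two rows would be 77.5% and 72.0%. Dilution under intention to treat is therefore a separate matter from the inflation slip, and correcting the slip would not settle it.

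**The case against.** The strongest reply is that the error hardly matters. Power of 78.7% against a stated 80% is a small gap, it arises only if the full 20% is lost, and 355 per arm keeps 294 up to 17.2% loss. This stands, and it is why the point is minor. It does not make the paragraph right: 294 and 20% do not give 355 by division, and even multiplication gives 353.

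A second reply concerns intention to treat. A reader might infer that because dropouts stay in the denominator, power must fall further below 78.7%. The article does not support that. It does not say whether dropout means stopping treatment or losing the birth outcome. Its Discontinuation criteria concern treatment only, and its Follow-up protocol traces pregnancies by visit, telephone and records to six weeks after delivery. If births are ascertained and the effect is undiluted, power with 355 per arm is 87.0%, above the target. The lower figures need assumptions of their own, and how dropouts are counted is commonly left to a full protocol or SAP that is not shown. Its absence here is no finding.

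That reply has a limit. The 87.0% case supposes that 20% dropout affects neither ascertainment nor the effect, which sits uneasily with having made an allowance at all. The range should be stated in full, without favouring either end.

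**Conclusion.** Wrong as written; severity minor. On the paragraph's own figures, a 20% allowance on 294 gives 368 per arm, while 355 leaves 284 and 78.7% power, 1.3 points below the stated 80%. This rests on reading the difference of 10 as percentage points (20% versus 30%), a two-sided 5% level, no continuity correction, and dropouts removed from the comparison, as the paragraph treats them. The first three are supported by the exact reproduction of 294.

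Two stronger conclusions should not be drawn. The trial is not seriously underpowered by this slip, and a null result would not be materially misread because of it. Nor is it established that the intention-to-treat analysis has lower power still: depending on the assumption, it lies anywhere from about 70% to about 87%.

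**What to change.** Correct the sample size paragraph without adding patients. Either of two statements would do:

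- 710 women randomised, with 20% dropout, leave 284 per arm and about 78.7% power for 20% versus 30%; or
- 294 per arm, and so 80% power, is kept only if dropout is at most about 17%.

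If a power for the intention-to-treat analysis is added, name the assumption and give the full range at 355 per arm: about 87% if all outcomes are known and the effect is undiluted, about 76% if the 20% who drop out count as no live birth, and about 70% if active-arm dropouts revert to the placebo rate.

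The change is to wording only. Enrolment had passed 500 at the time of writing (Trial status), and the target of 710 need not move. The cost is a slightly less favourable stated power.

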### Randomization and blinding

Eligible participants will be randomly assigned to one of the two study arms at a ratio of 1:1 according to an Excel table randomization list generated by a data coordinative center (DCC) staff who are independent of the study group, and the allocation will be input into the online database central grouping system. The random number list is kept strictly confidential by the DCC staff, and the researchers who are in charge of the enrollment have no access to the list.

Both the placebo and active component are manufactured by the pharmacist who was not involved in the subjects’ clinical management. Except for the active ingredients, the rest of the excipient and the appearance and odor are the same. The pharmacist packaged the DHEA and identical placebo capsules according to the randomization list and labeled the drug packs with subject numbers only. After screening the patients eligible for the entry, the researcher will log into the database to obtain the patient’s research number. Then the pharmacist will dispense the corresponding drug. The researchers and study participants will be blinded to the allocation until the end of the study.

#### Discontinuation criteria

Reasons for discontinuation of treatment may include, but are not limited to, the following: (1) participants become pregnant during the trial; (2) participants who have experienced some complications or serious side effects; (3) participants who do not comply with the DHEA were defined by using less than 80% or more than 120% of the prescribed amount; using prohibited drugs as described in the protocol, such as growth hormone and glucocorticoids; (4) participants who request to withdraw from the trial.

#### Intervention

The study will be conducted in following stages. After a recruitment period prior to baseline assessment and randomization, DHEA/placebo will be given to patients three times a day orally from the first day of their menstrual period for 4–12 weeks. After that, participants will undergo their IVF/ICSI cycle. Finally, a live birth rate follow-up will be performed.

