## Discussion

This study will compare the efficacy of 12-week DHEA treatment prior to IVF in POR. We plan to enroll 710 subjects from eight academic IVF centers in the Shandong Province. The result of this large multicenter randomized trial will provide level I evidence for the strategy of DHEA treatment for 12 weeks before IVF in poor ovarian responders.

DHEA treatment before IVF in POR has attracted increasing attention and has been considered promising for POR [25]. However, there are still great gaps in the literature to illuminate the risk/benefit ratio of this strategy, which includes multiple steps of treatment. Some research [20, 26–29] showed that DHEA supplementation improved the indicate of ovarian reserve, augmented ovarian response, and increased the clinical pregnancy rate. Meanwhile, the others [30–32] showed there were no such benefits. Some small-scale RCTs [28, 30, 31, 33] have been conducted to compare the efficacy of DHEA treatment before IVF. However, the varied definition of the patient population and primary outcome may result in the heterogeneity of comparisons. Additionally, the lack of rigorous design strategies, large scale, and high quality also make it difficult to reach any consistent conclusion [34].

This study is a multicenter randomized placebo-controlled double-blind clinical trial. In this research, we define poor ovarian responder according to the Bologna consensus [24], which is widely applied in clinical research after the recommendation. In 2003, the European Society of Human Reproduction and Embryology (ESHRE) recommended the singleton live birth rate as the evaluation index of assisted reproductive technology (ART) or non-ART reproductive outcome [35]. A healthy baby is the purpose of couples. That is the reason we chose live birth rate as the primary endpoint for this study.

Despite the lack of convincing evidence, DHEA supplementation is being used by more and more IVF centers around the world for POR. Large-scale, randomized placebo-controlled, blind, clinical trials are urgent to suggest physicians whether or not to use DHEA and how to use it. This study is expected to provide a reliable answer.

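### The objective and planned conclusion are for 12 weeks of DHEA, but the intervention as written is 4–12 weeks, so the primary comparison does not by itself support a 12-week conclusion

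*Protocol article*

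**What the plan says.** The protocol article gives the duration of study treatment in four sections.

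- **Abstract, Methods:** "Participants in these two groups will be given 4–12 weeks’ treatment of DHEA or placebo, respectively".
- **Intervention:** capsules are taken "three times a day orally from the first day of their menstrual period for 4–12 weeks", followed by the IVF/ICSI cycle.
- **Background, statement of purpose:** the aim is to "evaluate the effect of DHEA treatment for 12 weeks before IVF/ICSI on the live birth rate in infertile POR".
- **Discussion, first paragraph:** "This study will compare the efficacy of 12-week DHEA treatment prior to IVF in POR", and the result "will provide level I evidence for the strategy of DHEA treatment for 12 weeks before IVF in poor ovarian responders".

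Two other sections depend on the duration. Discontinuation criteria defines non-compliance as "using less than 80% or more than 120% of the prescribed amount". The Data analysis plan makes the primary analysis an intention-to-treat Pearson chi-squared comparison of live birth between the arms, with a secondary per-protocol analysis by treatment received. Neither section names a duration.

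**The concern.** The treatment under test is described in two ways that differ by up to a factor of three in weeks of exposure. Each version appears in more than one place, so this does not look like a slip of the pen. Nor is it a detail that a journal article leaves to the full protocol: the article states both versions, and a fuller document cannot make both of them the regimen.

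What is at stake is the question that the trial answers. A comparison of everyone randomised estimates the effect of the policy that was applied. If that policy is 4–12 weeks, the result belongs to that policy, while the article announces a conclusion about 12 weeks. The point matters more here because the Background reports that earlier randomised trials were criticised over, among other things, the duration of DHEA, and the Discussion says that such trials are needed to tell physicians how to use it.

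**Working it through.** **1. The sections side by side**

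| Section | Role | Duration |
|---|---|---|
| Background (purpose) | objective | 12 weeks |
| Discussion (two statements) | comparison and planned conclusion | 12 weeks |
| Abstract, Methods | summary of treatment | 4–12 weeks |
| Intervention | operative description | 4–12 weeks |

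The text shown does not present 12 weeks as a target with 4 weeks as a minimum, and gives no rule for who has a shorter course. The contradiction therefore cannot be settled from the article.

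**2. What the primary analysis estimates**

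The primary analysis compares the arms as randomised. Under the Intervention section this is a valid comparison of a 4–12 week DHEA policy with placebo. It would be a comparison of 12 weeks of DHEA only if 12 weeks were the assigned regimen.

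**3. The plan's sample size**

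Inputs from Determination of the sample size: control live birth rate 20%, a difference of 10 (read as percentage points, so 30%), 80% power, significance level 0.05 (taken as two-sided). Allocation is 1:1.

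n = [1.960·√(2p̄q̄) + 0.842·√(p₁q₁ + p₂q₂)]² / d²

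With p̄ = 0.25 and d = 0.10:

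n = [1.960·√0.375 + 0.842·√0.37]² / 0.01 = (1.2002 + 0.5119)² / 0.01 ≈ 293.2, rounded up to 294.

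The stated 294 per arm is reproduced, and its power is 80.1%. The section does not tie the 10-point difference to any duration.

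**4. Range of power (illustration only)**

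The share f of women with short courses, and the fraction r of the full effect that a short course gives, are assumptions. Neither is in the article. Taking 10 points as the effect of a full course:

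d = 0.10 × [(1 − f) + f·r]

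Power = Φ{[d√n − 1.960·√(2p̄q̄)] / √(p₁q₁ + p₂q₂)}, with n = 294 and p₂ = 0.20 + d.

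| Short-course share f | r = 1 | r = 1/3 | r = 0 |
|---|---|---|---|
| 10% | 80.1% | 74.8% (d = 9.3 points) | 71.9% (d = 9.0) |
| 25% | 80.1% | 65.6% (d = 8.3) | 57.0% (d = 7.5) |
| 50% | 80.1% | 48.0% (d = 6.7) | 30.5% (d = 5.0) |

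Worked cell (f = 25%, r = 1/3): d = 0.10 × (0.75 + 0.25/3) = 0.0833 and p₂ = 0.2833. Then [0.0833 × 17.146 − 1.1866] / 0.6025 = 0.402, and Φ(0.402) = 65.6%.

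**5. The compliance band**

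In weeks of full dosing, 80%–120% of a 4-week prescription is 3.2–4.8 weeks, and 80%–120% of a 12-week prescription is 9.6–14.4 weeks. The two bands do not overlap. The discontinuation criterion therefore depends on which duration the prescribed amount refers to.

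**The case against.** **The randomised comparison is sound.** Both arms follow the same schedule under blinding and are analysed as randomised. A trial of a 4–12 week policy is a legitimate trial. This stands: the fault lies in the wording of the aim and of the claimed conclusion, not in the test.

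**The durations given are not reported.** A reader might infer that the trial as run cannot inform a 12-week strategy, that a null result could not count against it and that a positive one could not count for it. The article does not support statements that absolute. If most women took about 12 weeks, the result would still say much about 12 weeks.

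**The compliance band does have a reference.** A reader might infer that a woman who completes 4 weeks could be judged 33% compliant and discontinued. That requires holding a woman prescribed 4 weeks to a 12-week amount, which no section says. The prescribed amount may be set for each patient, and the article refers to a protocol that may define it. What remains is that the term must match whichever duration is finally stated.

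**Loss of power is not shown.** A reader might infer that the trial is underpowered because of short courses. The 10-point difference may equally describe the 4–12 week policy, and power does not fall if short courses work as well as long ones.

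None of this removes the contradiction between the four sections.

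**Conclusion.** The point holds as a contradiction in the text with a consequence for the claim. As written, the article tests 4–12 weeks and announces a conclusion for 12 weeks. The intention-to-treat result will be valid for the first and will not by itself establish the second. The size of the gap cannot be given, because it depends on durations that the article does not report.

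The effect on power is likewise unknown. At 294 per arm it is 80.1% if short courses give the full effect, and lower under assumptions about their share and effect that nothing in the article confirms. The point does not rest on those figures.

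This should be fixed. It does not invalidate the design or the primary test.

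**What to change.** Before unblinding:

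1. Reconcile the abstract, the purpose statement in the Background, the Intervention section and the Discussion to one stated regimen. Which regimen is for the sponsor to decide; this review proposes none.
2. If the 4–12 week range stands, restate the objective and the planned conclusion as the effect of a 4–12 week policy, and remove the claim of level I evidence for a 12-week strategy.
3. Make the prescribed amount in Discontinuation criteria consistent with whichever duration is stated. The rule itself is the sponsor's.

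The cost is a change of wording and, if the range is kept, a narrower claim. Timing matters: if the target of the conclusion is settled only after the results are known, the choice could look driven by them.

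Recording an intended duration before randomisation is not requested. Trial status reports more than 500 of 710 women already enrolled, so it would reach fewer than 710 − 500 = 210. It would also presume that an intended duration exists at that point, which the article does not say.
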